### **Phase I pilot testing**

This initial pilot testing will be conducted with approximately 10 physicians (see letters of support) at Cleveland Clinic Main Campus in downtown Cleveland, OH and the Stephanie Tubbs Jones (STJ) Community Health Center, located in the underserved community of East Cleveland, OH. (The number of physicians may increase if necessary to achieve desired sample size.) Both facilities serve a wide range of middle-aged patients, with diversity by race/ethnicity and comorbidity (Table 1). ***Patient inclusion criteria:*** Age 45-70 years, established patient (so that model inputs are more readily available), appointment with a primary care physician, and  $\geq 2$  risk factors (tobacco use, overweight/obese, hypertension, hyperlipidemia, diabetes, alcohol misuse, depression, history of sexually transmitted infection, or being overdue for colorectal, cervical, breast, or lung cancer screenings). ***Exclusion criteria:*** Severely limited life expectancy (cancer, CHF, COPD, ESRD). ***Training:*** Outside of regular clinic time, study staff will lead provider training on shared decision making and use of visual aids, focusing on 3 key steps: informing patient that there are various options for their preventive care, providing more detail about options, and discussing patient preference to decide on a course of action. Providers will be encouraged, but not required, to participate in training. We also will discuss ways to probe patient values in the exam room (e.g., “Are you willing to change your lifestyle to prevent a serious health problem in the future? What kinds of things would you consider? How do you feel about blood tests and X-rays that may be less impactful on your health, but are easier to do?”).

Best practices for decision aids require a values clarification (e.g., helping patients to think about which aspects matter most to them) and explanation that a patient is free to choose nontreatment. (Source: National Quality Forum. National Standards for the Certification of Patient Decision Aids. Final Report. December 15, 2016.) Therefore, we have created written materials (attached) to explain that their provider would like to discuss some things about which there is no “right” answer; introduce shared decision making; explain that both patients and providers play important roles; their doctor wants them to participate; and prompts to ask questions. Based on provider and patient feedback that it is important not to overwhelm with too much information during the appointment, we may provide this information to patients with the mailed informational letter, shortly after check-in for their appointment, and/or shortly after they finish with their provider (before they leave).

| Table 1. Summary Statistics        |               |                    |            |
|-------------------------------------------|---------------|--------------------|------------|
| Patients aged 50-64 y seen in 2015 |               |                    |            |
|                                           |               | Main Campus | STJ |
| N patients                                |               | 7,550              | 2,567      |
| N wellness visits                         |               | 2,456              | 402        |
| Gender                                    | Female        | 58%                | 58%        |
| Race                                      | Black         | 47%                | 84%        |
| Smoker                                    | Current       | 17%                | 39%        |
| Obese (BMI $\geq 30.0$ )                  |               | 41%                | 47%        |
| BP                                        | $\geq 140/90$ | 9%                 | 13%        |
| LDL                                       | 100-159       | 40%                | 36%        |
|                                           | $\geq 160$    | 6%                 | 5%         |
| Diabetes Diagnosis                        |               | 29%                | 40%        |
|                                           | HbA1c $> 9$   | 4%                 | 7%         |
| Overdue: colorectal cancer screening      |               | 37%                | 46%        |
| Zip code median income $< \$25,000$       |               | 31%                | 61%        |
| Medicaid                                  |               | 5%                 | 44%        |

Simultaneous to Aim 1, we will develop a web portal on which a user may input all model parameters and receive the tailored decision aid. Following methods from prior research, we then will conduct practice runs (to simulate workflow) and iterative rounds of pilot testing (likely 3 to 4) in short bursts of approx. 2-4 weeks. To minimize risk of attrition, we will include only a subset of the approx. 10 providers in each round, so that each provider only participates once. (Providers may choose to continue based on interest.) Each week, the study team will identify eligible patients who have appointments with participating providers approx. 2-4 weeks later (obtained by data feed from our EMR group; our institution routinely uses this process.) Study staff will contact eligible patients by mail, telephone or in waiting rooms (see attachment). Study staff then will review the chart, manually enter model inputs, and distribute a printed copy of the tailored decision aid to each patient's providers. Additional copies will be provided on the day of appointment. Providers will be the research subjects. Providers will be asked to show each patient his/her individualized recommendations and engage in shared decision making about preventive care goals. At the end of the visit, a medical assistant or study staff will hand the patient a printed copy of the decision aid to take home, along with an after-visit summary that s/he already provides **Feedback:** We will seek feedback from participating providers. Feedback may be in whatever form is most convenient for each provider (oral, written, email, etc.). Additionally, we will inform patients that their doctor is participating in a research study, and ask patients if they would be interested in providing feedback in the form of a 10-15 minute survey. The patient will **not** be required to complete the survey. If the patient chooses to complete the survey, then s/he will receive \$25. We do not require any pre-specified number of patients to agree. We chose this method as a variant of prior work that has cluster randomized clinical practices to early vs. delayed intervention (where controls were patients in the delayed group before implementation), recognizing the non-randomized, exploratory nature of our study. For providers, our goal from feedback will be to create a tool that is easily understood, that providers are interested in using, and that providers believe improves the patient visit and facilitates shared decision-making. For patients who choose to complete the survey, outcomes measures (Appendix C) will include: use of shared decision making (Shared Decision Making-Q-9—e.g., “My doctor told me there are different options for preventive care”, “My doctor and I selected preventive care options together”) and plans for preventive care activity over the next 1 month and 6 months.

## **Phase II pilot testing**

As Phase I pilot testing winds down, the research team will conduct a subsequent phase of pilot testing that is broader and includes randomization. The protocol for Phase II pilot testing is the same as for Phase I, with the following exceptions:

1. Instead of just physicians, pilot testing may be conducted with any primary care provider (e.g., physicians, physician assistants, nurse practitioners, registered nurses),
2. Pilot testing may be conducted at any Cleveland Clinic internal medicine, community internal medicine, or family medicine department. There is no targeted number of practice sites or providers.
3. Shortly before each appointment at which the decision aid may be discussed, the visit will be randomized to “intervention” or “control.” During intervention appointments,

the individualized recommendations will be made available to providers as per Aim 1. During control appointments, the research team may still generate individualized recommendations but will not make them available to providers. Regardless of whether the appointment was intervention or control, the patient will still be informed that their doctor is participating in a research study, and we will ask patients if they would be interested in providing feedback in the form of a 10-15 minute survey, as per Aim 1. As with Aim 1, the patient will **not** be required to complete the survey.

4. Patients who choose to complete the survey will be notified that after their appointment, we may review their medical record to see which health care services they receive during the next 1 year. Providers will be similarly notified that we may review the medical records of their study patients. The purpose of this review is to see whether provider conversations had an impact on which preventive services were ultimately provided to patients. To ensure that patients are aware of this, we will only review the medical records of patients who chose to complete the survey. This process presents no more than minimal risk of harm to subjects and involves no procedures for which written consent is normally required outside the research context.
5. We will use a different survey from Phase I pilot testing. While Phase I pilot testing is primarily intended for general feedback on the design of individualized preventive care recommendations, Phase II pilot testing includes validated scales for patient feedback (e.g., the Shared Decision Making (SDM)-Q-9 scale and the Decisional Comfort Scale). The Phase II pilot testing survey uses a different version for males and females because some preventive services only apply to one sex (e.g., screen for cervical cancer).
6. Employees who participated in Phase I pilot testing will be eligible for participation in Phase II and will provide an updated information sheet if they are asked to participate. We attach a script for this discussion. Patients who participated in Phase I pilot testing will not be eligible for participation in Phase II.

Information sheets, a patient information letter and scripts for Phase II pilot testing are attached.

### Design aspects that apply to all pilot testing

We hypothesize that providers who utilized individualized, tailored recommendations will find that they facilitate discussions of preventive

care and shared decision-making. We hypothesize that patients who received individualized, tailored recommendations will change their intentions around preventive care (which services

**Figure 6.** Sample Questions for Provider Interviews (Draft, Appendix D)

|                                                                        |
|------------------------------------------------------------------------|
| What value did our approach add to the patient encounter?              |
| What was most/least helpful? How could it be improved?                 |
| Did the tool encourage shared decision making with patients? How?      |
| Are you inclined to use the tool in practice? Are there any obstacles? |
| How did it fit with clinical work flow? How might that be improved?    |
| What other information would be helpful?                               |

582 they intend to do in the next 1 month or 6 months). We also hypothesize that patients who  
583 receive the intervention will report use of shared decision making. We also will interview  
584 providers (Figure 6).

585 **Sample Size:** On average, a 1.0 FTE provider sees 8 eligible patients/week; our median FTE is  
586 0.5 (range: 0.2-1.0). As pilot testing, we do not require a pre-specified number of surveys to be  
587 completed. (We assume a baseline SDM-Q-9 mean and standard error of 31 and 9, respectively,  
588 on a 45 point scale.) An information sheet will be used for providers, and an additional  
589 information sheet will also be provided to patients stating that their doctor is participating in a  
590 research study. For patients who are interested in providing feedback, the information sheet will  
591 also describe the survey. The intervention is minimal risk because providers can ignore  
592 individualized recommendations, and providers retain discretion in ordering.

593 **Rapid Improvement:** Following each burst, the study team will review feedback and identify  
594 next steps. As needed, we will spend approx. 1-4 weeks improving use of the decision aid, the  
595 quality of shared decision making (from both patient and provider perspectives), and  
596 workflow before implementing the next round. Testing will stop after approx. 4 rounds or when  
597 feedback suggests that the process cannot be further improved in an exploratory study. The  
598 finished product will represent a tailored decision aid ready for wide-scale testing.

599 **Cognitive interviews:** Selected patients (particularly early in the study) may be asked to  
600 participate in cognitive interviews, to help the study team better understand opinions of the  
601 individualized preventive care recommendations. Because these interviews are likely to be short  
602 (10-15 minutes), the patients who participate in cognitive interviews will not receive additional  
603 compensation.

604 **Survey mechanics:** The surveys will be administered in RedCAP. Patients will be offered the  
605 opportunity to complete the survey immediately after their appointment, on a Cleveland Clinic  
606 computer. Alternatively, patients who prefer may complete the survey on their own computer,  
607 using the internet. In this case, we will provide patients with the web address and a code  
608 required by RedCap. This printout will come directly from RedCap, and an example is enclosed.  
609 Finally, if patients prefer, we can ask them the survey questions over the phone. Patients will  
610 have 3 business days after their appointment to complete the survey. Survey responses will be  
611 confidential, not anonymous, in order to allow researchers to know which patients completed the  
612 survey for mailing of gift cards. Answers to the survey questions will not be shared with  
613 patient's doctors; participants will be informed of confidentiality.

614 **Data storage:** Cleveland Clinic Center for Value-Based Care Research investigators will collect  
615 data as required by the studies discussed within the protocol. Patient data will be stored on site  
616 (in a secure REDCap database) and access will be controlled in accordance to Cleveland Clinic  
617 and HIPAA standards. Protected Health Information (PHI) will not be shared outside of  
618 Cleveland Clinic.

## Amendment 4

We will conduct pilot testing of the decision aid. Pilot testing will be conducted in multiple phases, an initial phase for basic feedback and a subsequent phase for more advanced pilot testing.

### **Phase I pilot testing**

This initial pilot testing will be conducted with approximately 10 physicians (see letters of support) at Cleveland Clinic Main Campus in downtown Cleveland, OH and the Stephanie Tubbs Jones (STJ) Community Health Center, located in the underserved community of East Cleveland, OH. (The number of physicians may increase if necessary to achieve desired sample size.) Both facilities serve a wide range of middle-aged patients, with diversity by race/ethnicity and comorbidity (Table 1). ***Patient inclusion criteria:*** Age 45-70 years, established patient (so that model inputs are more readily available), appointment with a primary care physician, and  $\geq 2$  risk factors (tobacco use, overweight/obese, hypertension, hyperlipidemia, diabetes, alcohol misuse, depression, history of sexually transmitted infection, or being overdue for colorectal, cervical, breast, or lung cancer screenings). ***Exclusion criteria:*** Severely limited life expectancy (cancer, CHF, COPD, ESRD). ***Training:*** Outside of regular clinic time, study staff will lead provider training on shared decision making and use of visual aids, focusing on 3 key steps: informing patient that there are various options for their preventive care, providing more detail about options, and discussing patient preference to decide on a course of action. Providers will be encouraged, but not required, to participate in training. We also will discuss ways to probe patient values in the exam room (e.g., “Are you willing to change your lifestyle to prevent a serious health problem in the future? What kinds of things would you consider? How do you feel about blood tests and X-rays that may be less impactful on your health, but are easier to do?”).

Best practices for decision aids require a values clarification (e.g., helping patients to think about which aspects matter most to them) and explanation that a patient is free to choose nontreatment. (Source: National Quality Forum. National Standards for the Certification of Patient Decision Aids. Final Report. December 15, 2016.) Therefore, we have created written materials (attached) to explain that their provider would like to discuss some things about which there is no “right” answer; introduce shared decision making; explain that both patients and providers play important roles; their doctor wants them to participate; and prompts to ask questions. Four possible versions are attached; we will try different versions and evaluate feedback until we find a preferred version. Based on provider and patient feedback that it is important not to overwhelm with too much information during the appointment, we may provide this information to patients with the mailed informational letter, shortly after check-in for their appointment, and/or shortly after they finish with their provider (before they leave). For patients who receive

| Table 1. Summary Statistics        |               |                    |            |
|-------------------------------------------|---------------|--------------------|------------|
| Patients aged 50-64 y seen in 2015 |               |                    |            |
|                                           |               | Main Campus | STJ |
| N patients                                |               | 7,550              | 2,567      |
| N wellness visits                         |               | 2,456              | 402        |
| Gender                                    | Female        | 58%                | 58%        |
| Race                                      | Black         | 47%                | 84%        |
| Smoker                                    | Current       | 17%                | 39%        |
| Obese (BMI $\geq 30.0$ )                  |               | 41%                | 47%        |
| BP                                        | $\geq 140/90$ | 9%                 | 13%        |
| LDL                                       | 100-159       | 40%                | 36%        |
|                                           | $\geq 160$    | 6%                 | 5%         |
| Diabetes Diagnosis                        |               | 29%                | 40%        |
|                                           | HbA1c $> 9$   | 4%                 | 7%         |
| Overdue: colorectal cancer screening      |               | 37%                | 46%        |
| Zip code median income $< \$25,000$       |               | 31%                | 61%        |
| Medicaid                                  |               | 5%                 | 44%        |

the values clarification before their appointment, we may provide their written individualized recommendations at that time and/or during their appointment.

Simultaneous to Aim 1, we will develop a web portal on which a user may input all model parameters and receive the tailored decision aid. Following methods from prior research, we then will conduct practice runs (to simulate workflow) and iterative rounds of pilot testing (likely 3 to 4) in short bursts of approx. 2-4 weeks. To minimize risk of attrition, we will include only a subset of the approx. 10 providers in each round, so that each provider only participates once. (Providers may choose to continue based on interest.) Each week, the study team will identify eligible patients who have appointments with participating providers approx. 2-4 weeks later (obtained by data feed from our EMR group; our institution routinely uses this process.) Study staff will contact eligible patients by mail, telephone or in waiting rooms (see attachment). Study staff then will review the chart, manually enter model inputs, and distribute a printed copy of the tailored decision aid to each patient's providers. Additional copies will be provided on the day of appointment. Providers will be the research subjects. Providers will be asked to show each patient his/her individualized recommendations and engage in shared decision making about preventive care goals. At the end of the visit, a medical assistant or study staff will hand the patient a printed copy of the decision aid to take home, along with an after-visit summary that s/he already provides ***Feedback:*** We will seek feedback from participating providers. Feedback may be in whatever form is most convenient for each provider (oral, written, email, etc.). Additionally, we will inform patients that their doctor is participating in a research study, and ask patients if they would be interested in providing feedback in the form of a 10-15 minute survey. The patient will **not** be required to complete the survey. If the patient chooses to complete the survey, then s/he will receive \$25. We do not require any pre-specified number of patients to agree. We chose this method as a variant of prior work that has cluster randomized clinical practices to early vs. delayed intervention (where controls were patients in the delayed group before implementation), recognizing the non-randomized, exploratory nature of our study. For providers, our goal from feedback will be to create a tool that is easily understood, that providers are interested in using, and that providers believe improves the patient visit and facilitates shared decision-making. For patients who choose to complete the survey, outcomes measures (Appendix C) will include: use of shared decision making (Shared Decision Making-Q-9—e.g., “My doctor told me there are different options for preventive care”, “My doctor and I selected preventive care options together”) and plans for preventive care activity over the next 1 month and 6 months.

## **Phase II pilot testing**

As Phase I pilot testing winds down, the research team will conduct a subsequent phase of pilot testing that is broader and includes randomization. The protocol for Phase II pilot testing is the same as for Phase I, with the following exceptions:

1. Instead of just physicians, pilot testing may be conducted with any primary care provider (e.g., physicians, physician assistants, nurse practitioners, registered nurses),
2. Pilot testing may be conducted at any Cleveland Clinic internal medicine, community internal medicine, or family medicine department. There is no targeted number of practice sites or providers.

- 707 3. Shortly before each appointment at which the decision aid may be discussed, the visit  
708 will be randomized to “intervention” or “control.” During intervention appointments,  
709 the individualized recommendations will be made available to providers as per Aim  
710 1. During control appointments, the research team may still generate individualized  
711 recommendations but will not make them available to providers. Regardless of  
712 whether the appointment was intervention or control, the patient will still be informed  
713 that their doctor is participating in a research study, and we will ask patients if they  
714 would be interested in providing feedback in the form of a 10-15 minute survey, as  
715 per Aim 1. As with Aim 1, the patient will **not** be required to complete the survey.  
716
- 717 4. Patients who choose to complete the survey will be notified that after their  
718 appointment, we may review their medical record to see which health care services  
719 they receive during the next 1 year. Providers will be similarly notified that we may  
720 review the medical records of their study patients. The purpose of this review is to  
721 see whether provider conversations had an impact on which preventive services were  
722 ultimately provided to patients. To ensure that patients are aware of this, we will only  
723 review the medical records of patients who chose to complete the survey. This  
724 process presents no more than minimal risk of harm to subjects and involves no  
725 procedures for which written consent is normally required outside the research  
726 context.  
727
- 728 5. We will use a different survey from Phase I pilot testing. While Phase I pilot testing  
729 is primarily intended for general feedback on the design of individualized preventive  
730 care recommendations, Phase II pilot testing includes validated scales for patient  
731 feedback (e.g., the Shared Decision Making (SDM)-Q-9 scale and the Decisional  
732 Comfort Scale). The Phase II survey may be conducted electronically, in writing, or  
733 by telephone. The written Phase II pilot testing survey uses a different version for  
734 males and females because some preventive services only apply to one sex (e.g.,  
735 screen for cervical cancer).  
736
- 737 6. Employees who participated in Phase I pilot testing will be eligible for participation  
738 in Phase II and will provide an updated information sheet if they are asked to  
739 participate. We attach a script for this discussion. Patients who participated in Phase  
740 I pilot testing will not be eligible for participation in Phase II.  
741

742 Information sheets, a patient information letter and scripts for Phase II pilot testing are attached.

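### Phase II randomises visits and bars only Phase I patients, so a patient who returns could be randomised into the other arm within the one-year record review

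*Supplement*

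**What the plan says.** The latest full protocol text is Amendment 4. Amendment 5 is an interview guide, and the amendment log records Amendment 6 as closing enrolment.

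- **Unit of randomisation** (Phase II pilot testing, item 3): "Shortly before each appointment at which the decision aid may be discussed, the visit" "will be randomized to “intervention” or “control.” During intervention appointments". Recommendations reach providers at intervention appointments and are withheld at control appointments. No allocation ratio is given.
- **Rules inherited from Phase I** (Phase II pilot testing, opening paragraph): "The protocol for Phase II pilot testing is the same as for Phase I, with the following exceptions". Six exceptions follow. None limits a patient to one randomised visit or carries the first allocation forward.
- **Eligibility** (Phase I pilot testing): "Age 45-70 years, established patient (so that model inputs are more readily available), appointment with a primary care physician, and" at least two listed risk factors. There is no once-only condition.
- **Bar on repeat participation** (item 6): patients who took part in Phase "I pilot testing will not be eligible for participation in Phase II". Nothing is said of patients already randomised in Phase II.
- **Record review** (item 4): for survey completers, after their "appointment, we may review their medical record to see which health care services" they receive over one year. The stated purpose is to see whether the conversations affected the services provided.
- **Timing** (Phase I pilot testing, inherited): "iterative rounds of pilot testing (likely 3 to 4) in short bursts of approx. 2-4 weeks". Breaks of about 1-4 weeks fall between rounds as needed (Rapid Improvement).

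**The concern.** Allocation attaches to a visit, but use of preventive services over a year attaches to a patient. If the same person has a control visit and later an intervention visit, the year of records after the first visit contains the exposure that the control arm is meant to lack. The protocol does not say which arm that history belongs to.

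Two further problems follow for the survey outcomes:

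- An intervention patient takes home a printed copy of the aid. A later visit allocated to control therefore yields a control survey from someone already exposed.
- Two surveys from one patient are correlated, and no rule says whether both count.

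At stake is the integrity of the only randomised comparison in the programme, chiefly for the one-year service-use outcome.

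**Working it through.** There is no stated figure to reproduce: Amendment 4 sets no sample size, effect size or power. The check has three parts.

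**1. Does any rule prevent re-randomisation?** Phase I eligibility, the six Phase II exceptions, the section on design aspects that apply to all pilot testing, Amendment 5 and the amendment log were read for one. None states a once-per-patient rule, a carried-forward allocation or a method for analysing repeat visits. Item 6 shows that repeat participation was considered, but it closes only the route from Phase I to Phase II.

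**2. Would a second visit fall inside the review window?** Inputs: 3 to 4 rounds of 2-4 weeks, with breaks of 1-4 weeks.

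- Shortest schedule: 3 × 2 + 2 × 1 = 8 weeks.
- Longest schedule: 4 × 4 + 3 × 4 = 28 weeks.

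Both are shorter than 52 weeks. On the planned schedule, any second randomised visit therefore falls within one year of the first.

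**3. How large could the effect be?** Assumptions not in the documents: independent 1:1 allocation at each visit, and a share f of patients with exactly one repeat randomised visit.

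The chance that a patient with k randomised visits appears in both arms is 1 − 2 × 0.5^k. This gives 50% for k = 2, 75% for k = 3 and 87.5% for k = 4.

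Now classify patients by first allocation. Of first-visit controls, f/2 later receive the aid. First-visit intervention patients stay exposed whatever follows. If late exposure gave the full one-year effect Δ, the control arm would gain (f/2)Δ, and the contrast becomes Δ(1 − f/2).

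| f (assumed) | Controls later exposed | Contrast remaining | Loss |
|---|---|---|---|
| 5% | 2.5% | 0.975 Δ | 2.5% |
| 10% | 5% | 0.95 Δ | 5% |
| 20% | 10% | 0.90 Δ | 10% |
| 40% | 20% | 0.80 Δ | 20% |

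For a given f with one repeat visit, these losses are upper bounds. A control exposed partway through has only the rest of the year in which to respond, and providers may ignore the recommendations.

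The survey is completed within 3 business days of the appointment (Survey mechanics). A survey completed after a first randomised visit is therefore not affected by later re-randomisation.

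**The case against.** The strongest reply is that one visit per patient was probably intended. The amendment log speaks of an index encounter, and item 4 reads naturally as one appointment, one survey and one following year. Rounds are short, and each provider is planned to take part in one round, so few patients would return to a participating provider while testing is active. The hypotheses concern provider views, patient intentions and reported shared decision making, not service use. The record review is optional and covers survey completers only. The Phase II information sheets and scripts are attachments that are not shown, so they cannot be checked.

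Much of this stands, and it limits the size and severity of the point. It does not close the gap. The log's wording is not an eligibility rule. Providers may continue if interested. Phase II also admits any type of primary care provider across the institution's internal and family medicine departments, with no target number of sites or providers. A patient could therefore return to the same provider or meet another participating one.

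A reader might infer three stronger things, none of which the documents support:

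- **That crossover is planned.** No section plans re-randomisation; the text leaves it open.
- **That repeat surveys would be analysed as independent.** Amendment 4 describes no analysis model, so the handling is simply unspecified.
- **That a particular loss, or a multiple of the sample size, can be stated.** Neither f nor the allocation ratio is given, and there is no target sample to inflate.

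**Conclusion.** The point holds as a gap in the randomisation rule. Followed literally, Amendment 4 allows one patient to enter both arms, and for such a patient the arm for the one-year service-use outcome is undefined. That conclusion needs no assumption about frequency.

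The size does. With f between 5% and 40%, 1:1 allocation, one repeat visit and full effect from late exposure, the loss of one-year contrast is at most 2.5-20%. The documents do not show where in that range f lies, or that it lies in it at all; it could be smaller. The survey outcomes are largely protected, except for a control survey that follows an intervention visit and for repeat surveys from the same patient.

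Severity: moderate. This is pilot testing with no power claim, and service use is not among its stated hypotheses. It is still worth correcting, because the randomisation rule itself creates the problem and the repair is small.

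**What to change.** State that each patient is randomised once, at the first eligible Phase II visit. To do so, add patients already randomised in Phase II to the exclusions in item 6, and check the weekly patient list against those already randomised. No separate rule carrying the allocation forward is then needed, since an excluded patient has no later study visit.

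The log records enrolment as closed, so the analysis rule matters most for patients already enrolled. For anyone randomised more than once, analyse the first randomised visit under its original allocation, count one survey per patient, and report how many were re-randomised and how many first-visit controls later received the aid. This settles arm membership and removes duplicates. It does not undo exposure that has already occurred, which is why those counts should be reported.

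The cost is one sentence in the protocol, one in the analysis description and a routine list check. The downside is that a few repeat visits are not used.
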